### Eligibility criteria

Patients with a clinical indication for orotracheal intubation at the participating sites will be eligible for inclusion. Patients will be enrolled upon meeting all inclusion criteria and none of the exclusion criteria, as outlined in table 1. The study sites will maintain continuous records of all patients who meet the inclusion criteria but are not enrolled in the study, along with the reasons for their exclusion, in compliance with the Consolidated Standards of Reporting Trials (CONSORT) guidelines.

**Table 1 t1:** Eligibility criteria

Inclusion criteria	Exclusion criteria
– Age > 18 years – Indication for orotracheal intubation for any reason	– Pregnancy – Know allergy to any of the study drugs (lidocaine, fentanyl, propofol, ketamine, or rocuronium) – History of bradycardia (heart rate < 50 bpm) or atrioventricular block without a pacemaker – Suspected intracranial hypertension – Intubation during cardiac arrest

D - Day; MAP - mean arterial pressure; MV - mechanical ventilation.

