### Outcomes

The study's primary outcome is the lowest MAP recorded within the first 10 minutes following the induction for intubation.

Secondary outcomes include:

–Average MAP within the first hour after induction.–Mortality within the first hour after induction.–Cardiac arrest within the first hour after induction.–Occurrence of severe hypotension, defined as systolic blood pressure (SBP) < 80mmHg, within 1 hour after induction.–Occurrence of severe hypoxemia, defined as peripheral oxygen saturation (SpO_2_) < 85%, within one hour after induction.–Time for successful intubation.

Tertiary outcomes include:

–The number of intubation attempts.–The highest HR within 1 hour after induction.–The total dose of vasopressors administered within the first 24 hours, using the noradrenaline equivalent dose.–Mean change in vasopressor dose (norepinephrine equivalent) from baseline to hour 1.–Ventilator-free days within the first 7 days, defined as the number of days on which individuals are able to breathe spontaneously without any invasive ventilatory assistance, ascribing zero days to those who die within 7 days.–Mortality at day 7.–ICU mortality.–Hospital mortality.

Safety outcomes will be assessed during the first 10 minutes following induction, and will include:

–Hypertension, defined as SBP > 180mmHg.–Laryngospasm, as reported by the physician in charge of intubation.–Bradycardia, defined as HR < 45 bpm.–Arrhythmias.–Bronchoaspiration, defined as the presence of gastric content aspirated into the airway during intubation.

All outcome data will be presented as specified on the electronic supplemental materials (Table 1S - Supplementary Material). The trial sequence is available in figure 1.

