### Data collection

Demographic characteristics, comorbidities, clinical data, and severity of illness will be collected at baseline for all patients (Table 2S - Supplementary Material). Additional data on the procedure characteristics will also be collected (Table 3S - Supplementary Material). During and after the procedure, hemodynamic data will be registered at the following time points: 1 minute before induction; every 2 minutes during the first 10 minutes after the administration of the study medication; every 5 minutes up to one hour after induction (Table 4S - Supplementary Material). Doses of vasoactive drugs will also be recorded. Any adverse events occurring within the first hour post-induction, including death, cardiac arrest, arrhythmias, bronchoaspiration, and laryngospasm, will be documented.

Patients will be followed until hospital discharge, censored at day 60^th^, to determine the need for mechanical ventilation up to day 7, vital status at day 7, in the ICU, and in the hospital. Patients who are withdrawn from the study for safety reasons (excluding those who withdraw consent) will be included in the analysis on an intention-to-treat basis.

Data will be collected via electronic forms using the RedCap platform and securely stored. The investigators will complete the forms, using specific passwords for access. Training will be provided for all personnel involved in the study to ensure high-quality data collection. The principal investigator will be available to answer any questions regarding form completion. Data consistency will be periodically reviewed, and any discrepancies will be addressed by contacting the sites for clarification and correction.

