For secondary binary and exploratory outcomes, logistic regression will be used, with the effect estimate expressed as odds ratios (ORs) and 95%CIs, with their respective p values. Deaths within the specified ranges will be considered zero free days for outcomes related to free days (ventilator-free days in 7 days). Logistic regression models for ordinal data will report proportional ORs. The frequency of adverse events will be expressed as counts and percentages, and comparisons will be made using the Chi-squared test for categorical variables. Secondary outcomes will not be adjusted for covariates.

For the primary outcome, a pre-specified subgroup analysis will evaluate the following groups: patients < 70 *versus* ≥ 70 years old; patients with a Sequential Organ Failure Assessment (SOFA) score < 8 *versus* ≥ 8 points; patients on vasopressor *versus* without vasopressors; and patients with acute respiratory distress syndrome (ARDS) *versus* those without ARDS. Each subgroup analysis will be performed using linear regression, adjusted for baseline MAP before induction, total vasopressor dose in the first 10 minutes, age, and a random patient intercept. Effect estimates will be reported as mean differences with 95%CIs for each subgroup, with respective interaction p values. We will not adjust for multiplicity.

We will consider a significant two-tailed p level ≤ 0.05. Analysis will be performed using R software in the available version (R Foundation for Statistical Computing), Vienna, Austria.

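### Severe hypotension, severe hypoxemia and hypertension are counted without regard to the pre-induction state, so states that were already present and persist dilute the drug comparison

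*Protocol article*

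**What the plan says.** **Entry.** Table 1 (Eligibility criteria) includes adults with "Indication for orotracheal intubation for any reason". None of the exclusions concerns oxygen saturation or blood pressure. The only one on rhythm is "History of bradycardia (heart rate < 50 bpm) or atrioventricular block without a pacemaker".

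**Outcomes.** Two of the secondary outcomes are "Occurrence of severe hypotension, defined as systolic blood pressure (SBP) < 80mmHg, within 1 hour after induction" and "Occurrence of severe hypoxemia, defined as peripheral oxygen saturation (SpO_2_) < 85%, within one hour after induction". The safety list contains "Hypertension, defined as SBP > 180mmHg" and an unqualified entry for arrhythmias; its window is given by "Safety outcomes will be assessed during the first 10 minutes following induction". None of these entries requires that the state was absent beforehand.

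**Analysis.** Under Statistical analysis, binary secondary outcomes go into logistic regression and adverse-event frequencies into a Chi-squared test. The section adds: "Secondary outcomes will not be adjusted for covariates". The primary outcome, lowest MAP, is adjusted for MAP before induction.

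**Baseline reading.** Under Data collection, "hemodynamic data will be registered at the following time points: 1 minute before induction". No stated definition or analysis of the threshold outcomes uses that reading.

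**The concern.** The population is one in which these states are expected at the outset. The Abstract names hypovolemia, vasoplegia and hypoxemia as features of such patients, the Interventions section provides for MAP below 65 mmHg before induction, and a subgroup with ARDS is planned. Some patients may therefore already have SpO2 < 85% or SBP < 80 mmHg, or less often SBP > 180 mmHg, when the drug is given. If the state is still there at a post-induction reading, the patient is counted as an event, although the drug did not bring it about.

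Such cases add events to both arms and carry little information on the contrast. The objective is to learn whether ketamine is safer, and the Introduction expects the two drugs to move blood pressure in opposite directions. In a safety comparison, attenuation is the unhelpful direction: a real difference is easier to miss. The trial is sized for MAP only, so these outcomes have little precision to spare.

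**Working it through.** **1. The plan's own figure.** Inputs from the sample size section: difference 10 mmHg, SD 20 mmHg, alpha 0.05 two-sided, power 90%, allocation 1:1.

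n per arm = 2 × (1.960 + 1.282)² × 20² / 10² ≈ 84.1, rounded up to 85, so 170 in total. Power at 85 per arm is 90.3% (90.0% by the t-test). The stated 170 reproduces. It concerns the primary outcome, which this point does not affect.

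**2. Dilution model.** Let q be the share of each arm already beyond the threshold before induction, and p the risk of a new event among the rest. If every pre-existing state persists after induction:

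- observed risk = q + (1 − q) × p
- observed risk difference = (1 − q) × (p₁ − p₂)
- observed OR = [r₁/(1 − r₁)] / [r₂/(1 − r₂)], where r is the observed risk

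The documents give neither q nor p. Assumptions: p = 25% versus 10%, and q from 0 to 30%.

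Example, q = 20%: r₁ = 0.20 + 0.80 × 0.25 = 0.40 and r₂ = 0.20 + 0.80 × 0.10 = 0.28. OR = (0.40/0.60) / (0.28/0.72) = 0.667/0.389 = 1.71.

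**3. Power.** Normal approximation for two proportions, with p̄ the mean of the two risks:

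power = Φ{ [|r₁ − r₂| − 1.96 √(2p̄(1 − p̄)/n)] / √([r₁(1 − r₁) + r₂(1 − r₂)]/n) }

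All patients: n = 85 per arm. At-risk patients only: n = 85 × (1 − q), rounded down, with risks of 25% and 10%.

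| q | Observed risks | Risk difference | OR, all patients | Power, all patients | At-risk n per arm | OR, at-risk | Power, at-risk |
|---|---|---|---|---|---|---|---|
| 0% | 25.0% vs 10.0% | 15.0 points | 3.00 | 73.4% | 85 | 3.00 | 73.4% |
| 10% | 32.5% vs 19.0% | 13.5 points | 2.05 | 52.1% | 76 | 3.00 | 68.5% |
| 20% | 40.0% vs 28.0% | 12.0 points | 1.71 | 37.8% | 68 | 3.00 | 63.6% |
| 30% | 47.5% vs 37.0% | 10.5 points | 1.54 | 28.2% | 59 | 3.00 | 57.5% |

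With 30% versus 15% assumed instead, the OR (written with the lower-risk arm on top) moves from 0.41 to 0.52 at q = 10% and 0.60 at q = 20%. All-patient power falls from 65% to 48% and 36%, against 60% and 55% in at-risk patients.

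**4. The other end of the range.** Suppose none of the q = 20% is still in the state after induction and none crosses the threshold again. The risks are then 0.80 × 0.25 = 20% and 0.80 × 0.10 = 8%, and the OR is (0.20/0.80) / (0.08/0.92) = 0.250/0.087 = 2.9. With 20% in the state beforehand, the OR therefore lies between 1.7 (all persist) and 2.9 (none persist), provided persistence is the same in both arms. The table is the full-persistence end.

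**The case against.** **Care before and during induction.** The Interventions section provides for pre-oxygenation, for vasoactive drugs when MAP is below 65 mmHg, and for dose adjustment during the procedure. A patient with SBP 75 mmHg or SpO2 80% may be corrected before induction. This stands. It makes the table an upper bound, although nothing in the article requires correction before the drug is given.

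**Persistence may depend on the drug.** Since the two drugs may act differently on blood pressure, a pre-existing state need not last equally long in both arms. This also stands: the pre-existing cases are not strictly a constant, and part of the all-patient contrast may be a real drug effect on recovery. It is a reason to keep the all-patient outcome.

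**The all-patient outcome is coherent.** Occurrence after induction in everyone analysed is a legitimate endpoint for a pragmatic trial. An at-risk analysis leaves out the most unstable patients, including one who starts at 84% and falls much further. At q = 30%, 0.30 × 170 = 51 patients would leave it. Replacing the endpoint would thus be a trade-off; adding to it is not.

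**Unseen material.** The supplementary tables are not shown and may hold operational detail. But the three threshold definitions are complete as printed, and the article itself rules out covariates for the secondary outcomes.

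**Stronger readings that the documents do not support.** A reader might infer that the arrhythmia rate will mostly describe the admission condition, with permanent atrial fibrillation counted in every such patient. However, Data collection lists arrhythmias among adverse events occurring after induction. The Safety and adverse events section counts complications as adverse only if they may be related to treatment, or are unexpected and not due to the underlying illness. A known chronic rhythm would hardly pass that filter, so the missing qualifier is mainly a wording gap. A reader might also infer bias toward one drug, but randomisation balances pre-induction states in expectation.

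**Conclusion.** The point holds for severe hypotension, severe hypoxemia and hypertension. Entry is open to patients already beyond these thresholds, the definitions ignore the pre-induction state, and the stated analyses do not account for it. The expected consequence is attenuation and lost precision in secondary and safety comparisons. The primary outcome is continuous and adjusted for baseline MAP, and neither it nor the sample size of 170 is affected.

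The size cannot be derived from the documents. At assumed new-event rates of 25% versus 10%, the OR of 3.0 becomes at worst 2.1, 1.7 or 1.5 for a baseline prevalence of 10%, 20% or 30%. This rests on full persistence, equal in both arms. If prevalence is low or most cases are corrected before induction, the effect is small. The added analysis is worth having because the baseline reading is already scheduled.

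**What to change.** Keep the three all-patient outcomes as defined. For each, add a pre-specified analysis among patients not already beyond the threshold at the reading 1 minute before induction, and report it beside the all-patient count. Alternatively, adjust the logistic model for the pre-induction value, stating this as an exception to the rule against covariates. Confirm that SpO2 is recorded at that reading, since Data collection names only hemodynamic data, and add it if not. Word the arrhythmia safety outcome as new-onset, to agree with the Data collection and Safety and adverse events sections.

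The cost is a wording change, at most one extra value from a monitor already attached, and a little analysis work. The at-risk analysis has a smaller denominator, which could matter if baseline prevalence is high (59 rather than 85 per arm at 30%). In this open-label trial the reading may also follow randomisation, though it precedes the study drug. Both are reasons to keep the all-patient count alongside.

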## INTRODUCTION

Rapid sequence intubation (RSI) is a series of actions aimed at promptly and safely securing a definitive airway via orotracheal intubation in patients at risk of aspiration,^(1)^ However, this procedure may result in hemodynamic disturbances.^(2,3)^

The RSI algorithm typically involves pre-medication, induction with a hypnotic agent, and neuromuscular blockade before laryngoscopy.^(4)^ The primary hypnotic agents utilized for this purpose include propofol and ketamine.^(5)^ Propofol, an alkylphenol derivative, is a highly lipophilic agent with potent hypnotic properties. However, it may negatively affect myocardial contractility and vasodilation, resulting in hypotension.^(4)^ In contrast, ketamine, a phencyclidine derivative, exhibits cardiovascular stimulant effects that may increase blood pressure, heart rate (HR), and cardiac output, leading to an increase in myocardial oxygen demand and a potential rise in intracranial pressure.^(6)^ However, in critically ill patients, physiological alterations induced by stress and disease processes may modulate the hemodynamic response to ketamine, and some studies have also reported hypotension associated with its use.^(7,8)^

Several studies have compared various RSI agents and their effect on hemodynamics,^(4)^ though most of these studies were conducted in operating rooms^(9)^ or emergency departments.^(10,11)^ Despite this, there remains a lack of randomized controlled trials comparing the use of propofol *versus* ketamine in critically ill patients. Prior studies comparing ketamine with etomidate^(12)^ or the combination of propofol and ketamine with etomidate^(4)^ found no significant differences in clinical outcomes.

Given this uncertainty, there is a need for controlled, prospective studies to evaluate its impact on complications associated with intubation. We hypothesize that ketamine is a safe alternative for RSI in intensive care unit (ICU) patients and may be associated with a lower incidence of hypotension and other complications compared to propofol. Therefore, the primary objective of this study is to assess whether ketamine is a safer alternative to propofol for RSI by reducing the incidence of hypotension during induction in critically ill patients.

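### Severe hypotension is counted for 1 hour but hypertension for only 10 minutes, from the same pressure readings, so the two opposing blood-pressure harms are measured unequally

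*Protocol article*

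**What the plan says.** All of the following is in the protocol article.

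- **Low pressure, primary outcome (Outcomes):** "The study's primary outcome is the lowest MAP recorded within the first 10 minutes following the induction for intubation".
- **Low pressure, secondary outcome (Outcomes):** "Occurrence of severe hypotension, defined as systolic blood pressure (SBP) < 80mmHg, within 1 hour after induction".
- **High pressure (Outcomes):** the safety list opens with "Safety outcomes will be assessed during the first 10 minutes following induction, and will include". Its first item is "Hypertension, defined as SBP > 180mmHg". The other four items are laryngospasm, bradycardia, arrhythmias and bronchoaspiration.
- **Heart rate (Outcomes):** a tertiary outcome is "The highest HR within 1 hour after induction".
- **Recording (Data collection):** haemodynamics are taken every 2 minutes to minute 10, then every 5 minutes to 1 hour. For events, "Any adverse events occurring within the first hour post-induction, including death, cardiac arrest, arrhythmias, bronchoaspiration, and laryngospasm, will be documented".
- **Expected drug effects (Introduction):** propofol is linked with hypotension, and ketamine "exhibits cardiovascular stimulant effects that may increase blood pressure, heart rate (HR), and cardiac output".
- **Use of the results (Discussion):** propofol could keep a place if it proves equally effective with fewer adverse events or a better safety profile.

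The article gives no reason for the different windows.

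**The concern.** The trial asks whether ketamine is the safer drug, and the Discussion expects readers to weigh safety profiles. The Introduction places the two ends of the blood-pressure range with opposite drugs. A fair weighing needs both ends counted over the same time, or a reason why not.

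As the outcomes are worded, an SBP of 75 mmHg at minute 25 is an event, and an SBP of 190 mmHg at minute 25, on the same monitor and the same form, is not. A reader comparing the severe hypotension row with the hypertension row would be comparing a 1-hour count with a 10-minute count.

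A smaller point of clarity goes with this. Arrhythmias, laryngospasm and bronchoaspiration are safety outcomes for 10 minutes and documented adverse events for 1 hour. The article does not say how the two counts relate in the results.

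**Working it through.** **1. The plan's own figure.** The only calculated figure in the article is the sample size: difference 10 mmHg, SD 20 mmHg, two-sided alpha 0.05, power 90%, 1:1 allocation. It reproduces at 85 per arm, 170 in total, with power 0.903 by the normal approximation and 0.900 by the noncentral t. It is not in dispute. It supplies the 85 per arm used in step 4.

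**2. Windows and scheduled readings** (Outcomes; Data collection).

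- By minute 10: readings at 2, 4, 6, 8, 10, which is 5.
- After minute 10: readings at 15, 20, ..., 60, which is 10.
- Total: 5 + 10 = 15.
- Time: 10/60 = 1/6 of the hour counts for hypertension, and 50/60 = 83% does not.
- Readings: 5/15 = 33% count for hypertension, and 10/15 = 67% do not. All 15 count for severe hypotension.

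The fraction by readings (a third) describes detection better than the fraction by minutes (a sixth), because the schedule is densest in the first 10 minutes.

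**3. Which outcomes are affected.**

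| Outcome | Window | Direction linked to a drug in the Introduction |
|---|---|---|
| Lowest MAP (primary) | 10 min | low pressure: propofol |
| SBP < 80 mmHg (secondary) | 1 hour | low pressure: propofol |
| SBP > 180 mmHg (safety) | 10 min | high pressure: ketamine |
| Highest HR (tertiary) | 1 hour | raised HR: ketamine |
| HR < 45 bpm (safety) | 10 min | none; opposite to the stimulant effect |
| Laryngospasm, arrhythmias, bronchoaspiration (safety) | 10 min | none |

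The mismatch that bears on the drug comparison is therefore one pair: SBP < 80 mmHg against SBP > 180 mmHg.

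**4. What a longer window could do to the hypertension contrast.** The article gives no hypertension rates, so those below are assumptions. Power for two proportions with n = 85 per arm, where p̄ is the mean of p1 and p2:

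Φ{ [|p1 − p2| − 1.96 √(2p̄(1 − p̄)/n)] / √([p1(1 − p1) + p2(1 − p2)]/n) }

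For 15% v 5%: [0.10 − 1.96 × √(2 × 0.10 × 0.90/85)] / √((0.1275 + 0.0475)/85) = 0.216, so power is 58.6%.

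(a) *Later events follow the drug.* Let f be the share of the 60-minute cumulative hazard that falls in the first 10 minutes. Then p60 = 1 − (1 − p10)^(1/f).

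| Assumed 10-min rates | Power at 10 min (also at 60 min if f = 1) | 60 min, f = 0.8 | 60 min, f = 0.5 | 60 min, f = 1/6 (constant hazard) |
|---|---|---|---|---|
| 10% v 5% | 23.4% | 27.9% | 40.4% | 79.2% |
| 15% v 5% | 58.6% | 67.9% | 85.9% | 99.8% |
| 20% v 10% | 44.6% | 52.5% | 70.3% | 95.5% |

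(b) *Later events are unrelated to the drug.* Start from 15% v 5% and add the same later risk b in each arm: p60 = 1 − (1 − p10)(1 − b).

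| b | 60-min rates | Difference | Power |
|---|---|---|---|
| 0 | 15.0% v 5.0% | 10 points | 58.6% |
| 10% | 23.5% v 14.5% | 9 points | 32.0% |
| 20% | 32.0% v 24.0% | 8 points | 21.1% |
| 30% | 40.5% v 33.5% | 7 points | 15.4% |

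The 1-hour window can sharpen or dilute the contrast, depending on event timing that the article does not give. That argues for reporting both windows, not for replacing one by the other.

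**The case against.** A reader might infer that the safety comparison is tilted towards ketamine, or that harms expected of ketamine get a sixth of the observation time. The case against that reading is strong.

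- Every outcome has the same window in both arms, so no ketamine-propofol contrast is biased. No composite or net-benefit analysis that would combine the two harms is described.
- The decisive low-pressure measure, the primary outcome, uses the same 10 minutes as hypertension.
- Highest HR, a stimulant effect expected of ketamine, is followed for the full hour.
- Of the five 10-minute safety outcomes, the Introduction links only hypertension to ketamine. "Bradycardia, defined as HR < 45 bpm" runs the other way, and the airway events and arrhythmias are attributed to neither drug.
- A peri-induction window is reasonable for a drug given as a bolus, and later events may have other causes.

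All of this stands, and the stronger reading falls with it. It does not explain why two ends of one vital sign, taken from the same readings, have different windows. Nor does the lack of a formal net-benefit analysis remove the problem, since the Discussion itself anticipates weighing safety profiles.

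**Conclusion.** The point holds as a minor reporting weakness. The two opposing blood-pressure harms are counted over different windows without a stated reason, and 10 of 15 scheduled readings can count for severe hypotension but not for hypertension. What is affected is the informal balance of harms and the completeness of the hypertension count, not the validity of any test. The count of 15 assumes that readings start 2 minutes after the study drug and follow the schedule. The consequence for results cannot be sized from the article; the power figures rest on assumed rates and show only that either direction is possible.

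Two further inferences are not supported. First, the first-hour documentation of arrhythmias, laryngospasm and bronchoaspiration does not contradict their 10-minute outcome window, because recording for longer than an outcome window is ordinary. It needs a sentence of explanation. Second, it cannot be said that late events are discarded. The Statistical analysis section reports and compares adverse event frequencies, where such events may appear if they meet the adverse event definition in the Safety and adverse events section. The presentation of outcomes is also left to a supplementary table that is not shown.

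**What to change.** 1. Report hypertension (SBP > 180 mmHg) and severe hypotension (SBP < 80 mmHg) each over both the first 10 minutes and the first hour, side by side and by arm. Keep the 10-minute hypertension count as the peri-induction safety outcome, and severe hypotension over 1 hour as the secondary outcome.
2. State in the Outcomes section how the 10-minute safety outcomes for arrhythmias, laryngospasm and bronchoaspiration relate to the first-hour adverse events in the Data collection section, and tabulate the first-hour counts as well.
3. Make the change before results by arm are seen, so that the choice of window cannot be questioned afterwards.

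Cost: a few sentences and some extra table rows. No new data are needed, because pressures and the named events are already recorded to 1 hour. The downside is that some events after minute 10 will be unrelated to the hypnotic and may dilute the 1-hour contrast, which is why the 10-minute count stays.
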